#### 1.2.2. Secondary Hypotheses

Participants who have higher data usage in the active VeNS group will have statistically significant changes in insomnia severity and improved quality of life after the 4-week treatment that will be maintained during the 12-week follow-up. There will be no change in insomnia and quality of life in the sham VeNS group immediately after treatment and at the post-treatment follow-up at 12-weeks.

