### 2.2. Subjects and Sample Size Estimation

Since the collaborative UK study is ongoing, we thus have to take reference of a similar CES study on GAD [23] on ‘Clinical effectiveness and cost minimization model of Alpha-Stim cranial electrotherapy stimulation in treatment seeking pts with moderate to severe GAD’. Participants in the CES group had a significant reduction in GAD-7 score (from baseline 15.77 (3.21) to 10.14 (4.86) (Cohen’s *d* = 1.3)) after 4 weeks of CES treatment.

Considering this trial is a sham-controlled trial, we hypothesize a large effect in the MS group. We used G*power version 3.1.9.7 (https://stats.oarc.ucla.edu/other/gpower/) (accessed on 1 April 2022) nto calculate the target sample size. With a statistical power of 99% and a statistical significance level at 0.05 to detect a large between-groups effect size of 1.3, each group will require 33 subjects. With an estimated attrition rate of 30% during the 12-week post-treatment follow-up, a total sample of 66 is required in this trial.

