### 2.7. Randomization, Allocation, Blinding and Masking

All consenting participants will be listed in alphabetical order according to their surnames and each participant will be assigned a unique identifier. An independent statistician will use a computer-generated list of random numbers (www.random.org) (accessed on 1 April 2022) to ensure concealment of randomization. Randomization will be conducted by an independent statistician off-site using a stochastic minimization program to balance gender, age, and GAD-7 scores of the participants. Block randomization with blocks of 10 (total: 7 blocks) will be used to allocate treatment groups. Participants from each block will be randomly assigned to the active VeNS groups or the sham VeNS groups in a 1:1 ratio. To avoid information flow, participants and research associates will be blinded to the group allocation to minimize potential contamination of the effects of VeNS or subject bias. The Principal Investigator will not be involved in data collection or pre- and post-VeNS measurements. Outcome measurements will be conducted by the research associates. Participants will be asked to guess the grouping (active VeNS vs. sham VeNS) when filling in the face-to-face post-test survey after finishing the 4-week interventions to determine the success of subject blinding [29].

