## 3. Statistical Analyses

All statistical analyses will be performed using the statistical software R for Windows (R version 4.1.0). Means and standard deviations (SD) for the continuous variables will be presented, while numbers and percentages for the categorical variables will be shown. A *p*-value < 0.05 is considered statistically significant. Sociodemographic differences between the VeNS group and the sham VeNS group will be analyzed using the chi-square test and t-test. If there are significant differences between sociodemographic factors, covariates will be considered as confounding variables in the analyses. Normality of the primary outcome (GAD-7) scores will be tested using the Shapiro–Wilk test for each combination of factor levels (group and time). A t-test will be used to test the baseline difference. Analysis of variance (ANOVA) with repeated measures will be used to test the group (between-subject factor), time (within-subject factor), and group x time interaction effects of the GAD-7 score between the VeNS group and the sham VeNS group. Post hoc comparisons between groups and time points will be conducted using a *t*-test with the Bonferroni correction. Normality of the secondary outcome scores will be tested using the Shapiro–Wilk test for each time point. For normally distributed outcomes, ANOVA with repeated measures will be used to determine whether the outcome scores are significantly different between pre-and post-test periods. For outcome scores that are normally distributed, a non-parametric Friedman test will be used to test the mean difference. A Cohen’s d effect size for each outcome will be calculated, where d = 0.2, 0.5, and 0.8, corresponding to small, medium, and large effect sizes, respectively. Participants’ total usage time will also be used to investigate the effectiveness of the VeNS on anxiety and total usage time will be used as a continuous covariate in a linear regression model for GAD-7 total score. Missing data will be managed with multiple imputation [36] by adopting the last observation carried forward (LOCF) method.

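### The secondary hypothesis predicts no change in insomnia and quality of life under sham, but the only analysis stated for these outcomes is a difference test, which cannot establish that

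*Protocol article*

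**What the plan says.** Section 1.2.2 (Secondary Hypotheses) has two halves. The first expects statistically significant change among higher-usage participants in the active arm. The second concerns the sham arm alone: "There will be no change in insomnia and quality of life in the sham VeNS group immediately after treatment and at the post-treatment follow-up at" 12 weeks.

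For the secondary outcomes, section 3 (Statistical Analyses) says that "ANOVA with repeated measures will be used to determine whether the outcome scores are significantly different between pre-and post-test periods", with a Friedman test as the non-parametric alternative. The general criterion is "A *p*-value < 0.05 is considered statistically significant". A Cohen's d is planned for each outcome, with the usual small, medium and large benchmarks, but no value of d is tied to the sham prediction. Missing data are to be handled by multiple imputation, described as adopting last observation carried forward (LOCF).

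Section 2.2 sizes the trial on the primary outcome only: "With a statistical power of 99% and a statistical significance level at 0.05" and "to detect a large between-groups effect size of 1.3, each group will require 33 subjects". It adds: "With an estimated attrition rate of 30% during the 12-week post-treatment follow-up, a total sample of 66 is required in this trial". By contrast, the primary hypothesis in section 1.2.1 does put a figure on the sham arm, a reduction in GAD-7 of less than 5%. Section 1.2.2 gives no such bound for the Insomnia Severity Index (ISI) or the SF-36.

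**The concern.** The sham half of the hypothesis is a null statement put forward for confirmation. A difference test starts from that null and can only reject it. With no margin and no confidence bound, the one stated result that could be cited in its favour is p of 0.05 or more, which is also what a small sample produces when a moderate change is present.

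What is at stake is a sentence in the trial report saying that sham left insomnia and quality of life unchanged, when the data may be compatible with a worthwhile improvement from expectation, attention or natural course. The wording of section 1.2.2 invites this, because it sets a significant change in one arm beside no change in the other.

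**Working it through.** **1. The plan's own sample size.** Inputs from section 2.2: d = 1.3, power 99%, alpha 0.05, attrition 30%. A two-sided two-sample t-test (noncentral t) needs 23 per group, with power 99.06%. Inflating for attrition: 23 / (1 − 0.30) = 32.9, so 33 per group and 66 in total. This reproduces the stated figures. A one-sided test gives 20, inflated to 29, and does not. The two-sided level is therefore used below.

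**2. Size of the sham arm.** Allocation is "active VeNS groups or the sham VeNS groups in a 1:1 ratio", so 33 are randomised to sham. After the stated attrition, 33 × 0.70 = 23.1, or about 23 completers at 12 weeks.

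**3. Chance of a non-significant result despite a real change.** Assumptions not in the article: a paired t-test within the sham arm, equal SDs at the two visits, and pre-post correlation r from 0.3 to 0.7. For a true change of δ baseline SDs:

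- standardised paired effect: dz = δ / √(2(1 − r))
- noncentrality: dz × √n, on n − 1 degrees of freedom
- miss rate: 1 − power at two-sided 0.05

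Example with δ = 0.5, r = 0.5, n = 33: dz = 0.5 / √1 = 0.50. Noncentrality = 0.50 × √33 = 2.87, against a critical t of 2.04. The miss rate is 20.5%.

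| r | δ = 0.5, n = 33 | δ = 0.5, n = 23 | δ = 0.3, n = 33 | δ = 0.3, n = 23 |
|---|---|---|---|---|
| 0.3 | 34.7% | 50.9% | 70.7% | 78.6% |
| 0.5 | 20.5% | 37.0% | 61.3% | 72.0% |
| 0.6 | 12.4% | 27.3% | 53.6% | 66.3% |
| 0.7 | 5.1% | 15.9% | 42.2% | 57.3% |

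**4. Which n applies.** At 4 weeks the stated attrition does not apply, because section 2.2 places it in the post-treatment follow-up; n is 33. At 12 weeks, LOCF would carry the 4-week value forward and keep 33 in the analysis. A simulation of a sustained 0.5-SD change, with 10 of 33 lost after the 4-week visit and that value carried forward, gives miss rates of 35%, 20%, 13% and 5% at the four correlations. These are the n = 33 rates up to simulation error. The n = 23 columns apply to a completers-only analysis. Rates close to them also arise if dropouts leave before the 4-week visit and baseline is carried forward (about 37% at r = 0.5).

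**5. What a non-significant result would leave open.** The 95% confidence interval half-width is t(0.975, n − 1) × √(2(1 − r)) / √n. At r = 0.5 this is 2.037 / √33 = 0.35 SD, or 2.074 / √23 = 0.43 SD. An observed sham change of 0.3 SD would be non-significant in both cases, with an upper limit of 0.30 + 0.35 = 0.65 SD or 0.30 + 0.43 = 0.73 SD.

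**The case against.** The strongest reply is that section 1.2.2 states an expectation, not a decision rule. A reader might infer that the plan will treat a non-significant sham result as proof of no change. The article does not say so; section 3 defines what counts as significant and is silent on what p of 0.05 or more means. This stands, and the point is limited accordingly. What remains is that the article offers no other criterion by which the sham prediction could be supported.

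A reader might also take 23 as the analysed number and conclude that dropout makes the prediction easier to confirm. The article does not support that as the main case: its missing-data rule is not completers-only, and under LOCF with dropout after the 4-week visit the n = 33 rates apply. At r of 0.6 or more those rates are modest for a 0.5-SD change, though not for 0.3 SD.

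A further tempting inference is that this wording would credit the active arm's entire pre/post change to the device. That risk comes mainly from the lack of a stated between-arm test for the secondary outcomes, which is a separate matter. Comparing the arms would remove it, although the statement about sham would still have no test able to support it.

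It is also true that section 3 names no sham-only test, so the rates above rest on an assumed one. Means, SDs and Cohen's d will be reported, so a sizeable sham change would be visible to a careful reader. That reduces the harm but does not supply a criterion.

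**Conclusion.** The point holds as a mismatch between a stated hypothesis and the stated test. It does not depend on what an unseen analysis plan might add, because both elements are in the article. With 33 in the sham arm, a true 0.5-SD change would go undetected in roughly 5% to 35% of trials and a 0.3-SD change in 42% to 71%. A completers-only analysis of about 23 would give 16% to 51% and 57% to 79%. These ranges rest on a within-sham paired test, equal SDs and correlations of 0.3 to 0.7, none of which the article gives. The matter is confined to secondary outcomes; the GAD-7 comparison and its sample size are untouched. It is worth correcting because it determines what the trial may say about its control arm and the correction is nearly free.

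**What to change.** In section 1.2.2, delete the sentence on the sham arm, or replace it with a hypothesis about the between-arm difference in change in ISI and in the SF-36 physical and mental component summaries. In section 3, add that the sham arm's mean change from baseline will be reported at each visit with its 95% confidence interval, as description, and that a non-significant sham change will not be interpreted as no change.

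The cost is one sentence in the hypotheses and one or two in the analysis section, with no new data or participants. The trial gives up a statement that sham had no effect. Keeping that statement would need a pre-stated margin and an equivalence test, with limited prospects. With an illustrative margin of ±0.5 SD of the change score (equal to the baseline SD at r = 0.5) and a true change of zero, two one-sided tests would succeed about 76% of the time with 33 participants and about 50% with 23.

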## 2. Materials and Methods

### 2.1. Trial Design

This is a four-week VeNS treatment on anxiety among adults in the general population. The trial design complies with the Consolidated Standards of Reporting Trials (CONSORT) statement [26]. Participants will be randomized into the active VeNS or sham VeNS group. All the participants will be informed about the randomization procedures and that they have a 50% chance of receiving the VeNS or the sham VeNS. This study will be conducted in accordance with the Declaration of Helsinki [27]. Both groups will be measured at the baseline (T1), immediately after the 4-week intervention (T2), and during a 3-month follow-up (T4) [23,28] (see Figure 1).

### 2.2. Subjects and Sample Size Estimation

Since the collaborative UK study is ongoing, we thus have to take reference of a similar CES study on GAD [23] on ‘Clinical effectiveness and cost minimization model of Alpha-Stim cranial electrotherapy stimulation in treatment seeking pts with moderate to severe GAD’. Participants in the CES group had a significant reduction in GAD-7 score (from baseline 15.77 (3.21) to 10.14 (4.86) (Cohen’s *d* = 1.3)) after 4 weeks of CES treatment.

Considering this trial is a sham-controlled trial, we hypothesize a large effect in the MS group. We used G*power version 3.1.9.7 (https://stats.oarc.ucla.edu/other/gpower/) (accessed on 1 April 2022) nto calculate the target sample size. With a statistical power of 99% and a statistical significance level at 0.05 to detect a large between-groups effect size of 1.3, each group will require 33 subjects. With an estimated attrition rate of 30% during the 12-week post-treatment follow-up, a total sample of 66 is required in this trial.

### 2.3. Recruitment

Samples will be recruited from our collaborative universities and Christian Family Services Centre (CFSC) in Hong Kong. A QR code flyer will be flagged up in communal areas in the Hong Kong Polytechnic University (HKPU), University of Hong Kong (HKU), and the Chinese University of Hong Kong (CUHK). Email invitations with the QR code poster will also be sent to all staff/students and alumni across different faculties/departments at HKPU, HKU, and CUHK. The project poster will also be advertised on the Facebook and Twitter of the School of Nursing, HKPU.

### 2.4. Eligibility Criteria

To obtain a homogenous sample, the inclusion criteria will be: (1) having a GAD-7 score > 10; (2) ethic Chinese, aged 18–60 years; (3) able to understand/read Chinese; (4) having an Insomnia Severity Index < 14; (5) able to provide written informed consent; (6) having Wi-Fi and Bluetooth network in iOS/Android mobile phones; (7) able to attend the face-to-face demonstration session for proper use of the MS device and return-demonstrate to research assistants in the training venue (Integrative Health Clinic, School of Nursing, The Hong Kong Polytechnic University; (8) willing to engage with the project team on a weekly basis via zoom meetings/WhatsApp/telephone to ensure compliance, proper usage of the MS device and report any technical issues; (9) not undergoing any extreme lifestyle changes that may impact on sleep quality (e.g., dietary changes/increase/decrease exercise levels) throughout the study period; (10) not taking any prescribed/over the counter anxiolytics.

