### 1.1. Objectives

The aims of this study are (1) to evaluate the efficacy of VeNS on anxiety severity on community-dwelling adults in Hong Kong and (2) to examine the association between VeNS data usage, anxiety symptom severity, insomnia severity, and quality of life.

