#### 2.12.2. Secondary Outcomes

##### Insomnia Severity

Insomnia will be assessed using the Chinese version of the Insomnia Severity Index (ISI) which consists of 7 items measuring the day and night symptoms of insomnia in individuals. This ISI consists of seven items (1: perceived difficulty; 2: falling asleep; 3: time of awakening; 4: satisfaction with current sleep pattern; 5: interference with daily functioning; 6: noticeability of others’ impact on lack of sleep; 7: degree of perceived distress/concern caused by the sleep problem). Subjects will rate each question on a 4-point Likert scale (0–3); score ranges from 0–28, with 15–21 indicating moderately severe insomnia. ISI has been used in the Chinese population with good psychometric properties, with Cronbach’s alpha 0·81 and item-to-total correlations in the range of 0.34–0.67 [33].

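### The entry cap of ISI below 14 excludes the protocol's own moderately severe insomnia band, although change in insomnia is a secondary hypothesis; the two need reconciling

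*Protocol article*

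**What the plan says.** Section 2.4 of the protocol article lists as an inclusion criterion "4) having an Insomnia Severity Index < 14". The only reason offered covers the whole list: "To obtain a homogenous sample, the inclusion criteria will be: (1) having a GAD-7 score > 10". Section 2.6 makes the ISI a screening instrument alongside the GAD-7, so the limit will operate in practice.

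Section 2.12.2 (Insomnia Severity) describes the scale: "score ranges from 0–28, with 15–21 indicating moderately severe insomnia". It names no other band.

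Insomnia is also something the trial sets out to study. Objective 2 in Section 1.1 is "to examine the association between VeNS data usage, anxiety symptom severity, insomnia severity, and quality of life". Section 2.12 repeats insomnia severity among the secondary objectives. The secondary hypothesis in Section 1.2.2 is directional between arms: "Participants who have higher data usage in the active VeNS group will have statistically significant changes in insomnia severity and improved quality of life", to be maintained at 12 weeks, while "There will be no change in insomnia and quality of life in the sham VeNS group".

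**The concern.** The two symptom criteria point in opposite directions. A GAD-7 score above 10 leaves room for the primary outcome to fall. An ISI below 14 takes room away from a secondary outcome that is also expected to fall. Homogeneity does not explain why a variable whose change and associations are to be measured should be restricted at entry, and the document does not discuss the tension.

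Three things are at stake, all on the secondary outcome:

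- **Sensitivity.** Lower starting scores leave fewer points to lose, so a given proportional benefit is a smaller absolute difference from sham.
- **Associations.** Any association in objective 2 that uses baseline ISI is computed over a narrowed range.
- **Scope.** Whatever the ISI result, it applies to anxious adults with ISI below 14, whereas the stated target is anxious adults in the general population.

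A restricted baseline cannot be repaired at the analysis stage, so this should be settled by amendment.

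**Working it through.** **1. The criterion against the band.** ISI scores are integers, so a score below 14 means 0–13. The stated band is 15–21 on a 0–28 scale. The overlap between 0–13 and 15–21 is empty. A score of 14 and all scores from 15 to 28 are excluded.

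**2. The plan's own sample size (GAD-7).** Inputs from Section 2.2: d = 1.3, power 99%, alpha 0.05 (two-sided assumed), attrition 30%. A two-sample t-test needs 22.75, so 23 per group; 23 / 0.70 = 32.9, so 33 per group and 66 in total. The stated figure reproduces. None is given for ISI. With these numbers, the smallest standardised difference detectable at 80% power is 0.70 (33 per arm) or 0.84 (23 completers per arm).

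**3. Whom the cap removes (illustration).** Assumption, not in the document: screening ISI is roughly normal with SD 5 and mean *m* between 11 and 15. With a continuity correction, the share excluded is 1 − Φ((13.5 − *m*)/5). The enrolled mean and SD are those of the normal truncated to −0.5 to 13.5.

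| Assumed mean | z | Excluded | Enrolled mean | Enrolled SD |
|---|---|---|---|---|
| 11 | 0.5 | 31% | 8.6 | 3.2 |
| 13 | 0.1 | 46% | 9.4 | 3.0 |
| 15 | −0.3 | 62% | 10.0 | 2.7 |

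**4. Range restriction.** With u = enrolled SD / 5, a full-range correlation r becomes r·u / √(1 − r² + r²u²). For an assumed r = 0.5 between baseline ISI and another variable, the result is 0.35 (u = 0.65) falling to 0.30 (u = 0.54). This concerns baseline ISI only.

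**5. Power for the ISI comparison (illustration).** Assumptions: follow-up SD 5, no change under sham, two-sided 0.05, two-sample t-test. Power is shown for 23 and 33 per arm.

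| Baseline | Active-arm fall | Points | d | Power (23 to 33 per arm) |
|---|---|---|---|---|
| 9 | 30% | 2.7 | 0.54 | 0.43 to 0.58 |
| 16 | 30% | 4.8 | 0.96 | 0.89 to 0.97 |
| 9 | 50% | 4.5 | 0.90 | 0.85 to 0.95 |

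**6. Sensitivity to the SD.** If the follow-up SD also shrank, say to 3, the 2.7-point fall would be d = 2.7 / 3 = 0.90, with the same power as the last row (0.85 to 0.95). The loss therefore turns on an SD that the document does not give.

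**7. A related inconsistency.** Section 2.12.2 also says "Subjects will rate each question on a 4-point Likert scale (0–3", inclusive. Seven items scored 0–3 give a maximum of 7 × 3 = 21, whereas 0–28 requires 7 × 4. What a limit of 14 means depends on which scoring is used.

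**The case against.** The strongest defence is that the cap may be deliberate. Anxiety is the primary outcome, the criteria are introduced as a way to get a homogeneous sample, and criterion 9 also controls influences on sleep. Limiting comorbid insomnia is a defensible choice at some cost in generalisability. This stands: the document does not show whether the inequality is reversed or intended, and a reader who infers a typing error goes beyond the text.

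A reader might also infer that the cap leaves nobody in whom the insomnia hypothesis could be shown. The document does not support that either. People scoring up to 13 can improve, no passage says that a score below 14 means no insomnia, and a halving from 9 keeps good power even at SD 5. Section 1.2.2 predicts change in severity among higher users; it does not predict response or remission in people with clinical insomnia.

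The introduction's remark that untreated anxiety may come to affect sleep gives no ISI distribution, so it cannot show how many candidates the cap removes. Follow-up ISI is not capped, so the range-restriction argument reaches only the analyses that use baseline ISI.

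What the defence does not answer is the missing reconciliation. A general appeal to homogeneity does not explain restricting a variable that the trial hypothesises will change.

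**Conclusion.** The conflict of purpose is established from the text alone: entry is limited to ISI 0–13, the moderately severe band starts at 15, and insomnia change is a stated secondary hypothesis. The cap excludes the people in whom a benefit could most readily be shown, leaves less room for ISI to improve and restricts its baseline range.

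The size is not established. The exclusion share of 31–62% and the drop in power from 0.89–0.97 to 0.43–0.58 rest on assumed means, SDs and proportional effects. The power loss largely disappears if the fall is 50% or if the follow-up SD is near 3. The primary GAD-7 analysis and its sample size are untouched. This is a moderate point about one secondary outcome and does not threaten the trial's main conclusion.

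**What to change.** Reconcile Section 2.4 with Sections 1.1, 1.2.2 and 2.12 by amendment. The choice between the two routes is the sponsor's:

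- **If the direction or the cap is unintended,** correct or remove criterion 4.
- **If it is deliberate,** state the reason, treat the ISI hypothesis as exploratory, and limit the insomnia conclusion to anxious adults with ISI below 14.

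In either case, specify that ISI is compared between arms with adjustment for baseline ISI, and settle the item scoring (0–3 or a 28-point total) so that the threshold has one meaning.

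The cost is one eligibility line or one hypothesis line, plus one sentence in Section 3. No new procedure is needed, because ISI is already collected at screening and baseline. The downside is a somewhat less homogeneous sample if the cap goes, or a narrower secondary claim if it stays.
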